**I Study Objectives**

**Primary Objective**

To describe the gut microbiota in patients with congenital chloride diarrhea (CLD).

**Secondary Objectives**

To study the effects of oral butyrate on the diarrhea and the gut microbiota.

**II Background and Rationale**

**Background on Disease**

A rare autosomal recessive disease congenital chloride diarrhea (CLD; OMIM #214700) is caused by mutations in the *solute carrier family 26 member 3* (*SLC26A3* alias *DRA*) gene on chromosome 7q22.3-31.1 ^1,2^. *SLC26A3* encodes for a major apical epithelial chloride-bicarbonate exchanger of the terminal ileum and colon ^3^. While options to resolve chronic diarrhea are missing, oral salt substitution with sodium and potassium chloride allows favorable outcome in CLD and prevents complications such as chronic volume and electrolyte depletion and kidney disease ^4,5^.

**Study Rationale**

For unknown reason, CLD subjects are prone to inflammatory bowel disease (IBD) ^4^. Whether gut microbiota is affected in CLD, or plays a role in CLD-associated IBD, remains unknown. We and others previously found that oral administration of short-chain fatty acid (SCFA) butyrate, the most essential end-product of bacterial carbohydrate fermentation in the colon and the principal nutrient for colonocytes ^6^, reduces the diarrhea in some patients with CLD ^7-9^. While these individual responses are poorly understood, luminal butyrate might increase intestinal sodium chloride and fluid reabsorption by modulating colonic epithelial ion transport ^6^. Collectively, these data prompted us to design this study on the gut microbiota and the potential modulatory effects of butyrate in patients with CLD.

**III Study Design**

This prospective cohort study involves the following parts:

1. Study visit, laboratory testing, and recording of intestinal symptoms, quality of life, and food diary
2. 3-week follow-up for all participants and collection of fecal samples once a week
3. 3-week voluntary trial with oral butyrate and collection of fecal samples once a week

**IV Selection and Enrolment of Participants**

**Background**

Potential participants will be selected among the Finnish CLD patients based on previous studies of the CLD cohort and from the records of the university hospitals.

**Inclusion Criteria**

Inclusion criteria are: age 2-60 years and the possibility to collect fecal samples once a week.

**Exclusion Criteria**

Exclusion criteria are: infection at the study entry or use of antibiotics during the previous 3 months.

**V Study Intervention**

**Interventions, Administration, and Duration**

The short-chain fatty acid butyrate is available as a supplement in the form of capsules. One capsule (BioCare® Butyric Acid; Biocare Ltd, Birmingham, UK) contains 605 mg of butyric acid. Targeted dose of butyrate is 100 mg/kg/day, divided in two daily doses, for 3 weeks.

**Sample Collection and Analyses**

Blood tests will include plasma levels of sodium, chloride, and potassium, venous blood gas analysis, blood count, creatinine, cystatin C, urea, and C-reactive protein (CRP). Urine level of chloride, glomerular filtration rate (GFR), and fecal calprotectin will be measured. All these measurements will be performed by the laboratories of the university hospitals. Serum samples will be stored for later analyses of inflammatory markers. Buccal swabs will be collected for the extraction of genomic DNA.

After home-based fecal sample collection, the samples will be immediately put in the freezer (-20°C) and thereafter, will be transferred into our research laboratory and stored long-term at -70°C. Fecal samples will be prepared for DNA extraction and microbiota analyses. Moreover, we will perform analyses for water content, total protein, intestinal alkaline phosphatase (IAP) activity, total immunoglobulins, and methylglyoxal-derived hydroimidazolone-1 (MG-H1). In-house samples or previous data from IBD subjects and healthy controls will be utilized as control populations in the analyses.

**VI Study Procedures**

**Schedule of Evaluation for Patient Population**

The study will be conducted in 2018 under supervision by the Children´s Hospital.

All participants will be examined at the study entry (time point 0, baseline). Data on participants’ health, intestinal symptoms, and diet will be recorded, and quality of life assessed based on the protocol as described previously ^10^. Their blood, urine and fecal samples will be collected. Thereafter, the patients will provide fecal samples once a week after 1, 2, and 3 weeks (time points 1, 2, and 3).

After the 3-week follow-up of all patients, patients can participate in a voluntary trial with oral butyrate. The subjects attending the butyrate trial will be followed up for another 3 weeks and they will collect fecal samples once a week at 4, 5, and 6 weeks from the baseline visit. Data on participants’ health and intestinal symptoms will be recorded during and after the butyrate trial. After the butyrate trial, blood and urine samples will be collected.

**Study Visit**

The participants will be met by a clinician for physical examination at the study entry (time point 0, baseline). The practical aspects and risks of the study will be discussed, oral and written information given, and any questions related to the study design and sampling answered. Demographic data will be extracted from the electronic medical records.

**Questionnaires**

Before the study entry, all participants will complete an internet-based survey (or a paper form) describing their overall health and medication, antibiotic use within the past 6 months, probiotic use, alcohol drinking, smoking habits, travel history, household pet ownership, intestinal symptoms, stool frequency, basic data on their diet, and quality of life. Moreover, their physical, social, emotional, and overall quality of life will be measured with a visual analog scale (VAS, from 1 to 7) by questionnaires as described ^10^. During the 3-week follow-up, and during and after the butyrate trial, the patients will fill once a week another internet-based questionnaire describing their intestinal symptoms, salt substitution, use of butyrate, and any changes in their health or well-being during the study.

**Dietary Data Collection**

The patients will keep a food record for 3 subsequent days before the first scheduled appointment at the study entry. A trained nurse will check the food records upon returning for possible omissions and controversies with the help of a picture booklet. A dietitian will record the food records with a software (AivoDiet, Aivo Finland Oy, Turku, Finland) that utilizes a national database of foods. The use of dietary supplements will be queried in the food records and their compositions will be checked from the manufacturers.

**VII Risks and assessments**

**Risks**

Butyrate supplement is considered safe, is freely available, and approved as a supplement. This compound involves no safety issues or side effects that might cause significant risks for the participants. In terms of laboratory testing, there are no risks or harms other than sampling and data might also be relevant for the follow-up and treatment of CLD.

**Benefits**

It is possible that attending this study will not be of direct benefit for a single participant. However, the results of the project may influence the development of new treatments and follow-up recommendations that benefit the entire population of patients with CLD.

**VIII Statistical Considerations**

**Sample Size**

The sample size will be limited for the rarity of CLD. This might cause bias in analyses and small but real differences in the gut microbiota or effects of butyrate may not be detectable.

**Data Analyses**

Data analyses will be carried out by following the clinical standards of the participating hospitals. For microbiota and fecal biomarker analyses, state-of-the-art methods will be utilized in the research laboratory of the study team.

**IX Data Collection**

**Data Collection and Management**

Because of the limited number of participants, the same study nurse and clinician will meet all the participants.

**Quality Assurance**

All participants will be met by the same personnel and the laboratory analyses will be performed either in the laboratories of the university hospitals or of the study team. This ensures following the same protocols and similar handling for all samples and data.

**X Participant Rights and Confidentiality**

**Institutional Review Board Review**

Study protocol has been approved by the ethics committee of the Hospital District of Helsinki and Uusimaa (HUS/895/2017).

**Participant Confidentiality and Security**

Information about the sample and the donor is processed only by the research personnel in accordance with the data security requirements for confidential data. Data protection is secured by encoding the samples, which means that your information or any personal data cannot be detected from the results of this study or from the reports or publications. Therefore, individual results from this research project will not be reported to participants. The results from this research project will be published in peer-reviewed international journals.

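### The rule against reporting individual results to participants is too broad: as worded it also covers the 12 clinical measures run by the hospital laboratories

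*Protocol*

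**What the plan says.** Protocol section X, under Participant Confidentiality and Security, explains that samples are encoded so that nobody can be identified from results or publications. It then concludes: "Therefore, individual results from this research project will not be reported to participants". The only words that limit its scope are those tying it to this research project. No type of result is exempted.

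Section III (Study Design) makes laboratory work a component of the study; the first part is described as "Study visit, laboratory testing, and recording of intestinal symptoms, quality of life, and food diary".

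Section V, under Sample Collection and Analyses, sets out two streams. One is a panel of blood tests, followed by "Urine level of chloride, glomerular filtration rate (GFR), and fecal calprotectin will be measured", all run by the university hospital laboratories. The other is research work by the study team on fecal samples, together with serum kept for later use and buccal swabs for DNA.

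Section VII, under Risks, adds that the laboratory data may have value for the patients' own follow-up and treatment.

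**The concern.** The hospital tests belong to the project, so a rule on results of the project reaches them unless it says otherwise. They are ordinary clinical measurements with direct relevance to this disease. Section II describes patients with congenital chloride diarrhea as predisposed to inflammatory bowel disease, and names loss of fluid and electrolytes and renal disease as complications that salt substitution prevents. Under Inclusion Criteria, participants may be as young as 2 years, so for many of them a guardian would need to be told.

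If staff followed the sentence to the letter, a participant or guardian would not be told of an abnormal potassium, GFR or calprotectin found in the study. This is a matter of participant safety and participant rights. It does not bear on any estimate.

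**Working it through.** The protocol gives no figure to reproduce here. The check is a count of what the sentence covers and a comparison of sections.

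**Step 1: hospital-laboratory measures (section V, Sample Collection and Analyses).**
- Blood: sodium, chloride, potassium, venous blood gas, blood count, creatinine, cystatin C, urea, CRP = 9.
- Other: urine chloride, GFR, fecal calprotectin = 3.
- Total: 9 + 3 = 12.

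**Step 2: research stream (same section).** Microbiota, fecal water content, fecal total protein, IAP activity, total immunoglobulins and MG-H1, plus stored serum and buccal DNA. The last two are stored or extracted material for which no specific assay is yet fixed.

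**Step 3: link to the complications named in section II.** The grouping is mine, not the protocol's.
- Electrolytes and volume: sodium, chloride, potassium, blood gas, urine chloride = 5.
- Kidney function: creatinine, cystatin C, urea, GFR = 4.
- Inflammation: CRP, calprotectin = 2.
- Sum: 5 + 4 + 2 = 11 of the 12. Blood count is general.

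These counts show what kind of result falls under the wording. They do not measure risk, because the protocol does not say how often abnormal values are expected.

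**Step 4: the sections side by side.**
- Study Design and Sample Collection and Analyses place the 12 measures inside the project.
- The confidentiality sentence withholds the project's individual results from participants, without exception.
- Risks presents the laboratory data as potentially useful for care. That use requires the data to reach the patient or whoever treats the patient.

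The literal rule and the Risks statement fit together poorly. They fit well if the rule is confined to the coded research assays, but the sentence does not say so, and no other section of the protocol gives a rule on reporting results to participants.

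**The case against.** The strongest reply is that context already supplies the limit. The paragraph is about encoding, and the sentence is drawn as a consequence of it, so its natural subject is results from coded samples. Nothing says that the hospital tests are coded. The Risks statement would make little sense if hospital results were to be kept from patients. One clinician examines every participant (Study Visit; Data Collection and Management), and the sentence does not bar that clinician from seeing a result or acting on it, which would normally mean contacting the patient or guardian. The consent material is not at hand and may state the terms for returning results.

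Most of this stands. It makes the narrow reading the likelier intent and rules out any claim that results are in fact withheld. It does not supply the missing words: the one rule the protocol states on the matter is unqualified, and no instruction to pass on abnormal results sits beside it.

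A reader might infer three stronger things, none of which the document supports.
- That participants are left uninformed by design. The protocol shows only wording that permits this reading.
- That the sections on quality assurance, data analysis or sample scheduling confirm one reporting rule for hospital and research results. Those sections deal with consistency, analysis and timing, not with reporting.
- That the appeal to encoding is itself a defect of consequence. It is a weak reason, since section X, under Study Discontinuation, promises to stop using a withdrawn person's samples and so implies that they can be traced. But removing that reason alone would change nothing the trial does, and not returning research assays may be right on other grounds.

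**Conclusion.** The point holds as an over-broad rule. As worded, the non-reporting sentence includes 12 hospital-laboratory measures that it probably was not meant to include, and this is in tension with the protocol's own statement that laboratory data may serve care. The possible consequence for safety depends on the literal reading being followed; the protocol does not show that it would be. The conclusion assumes only that the hospital tests are part of the project, which Study Design and Sample Collection and Analyses support. Nothing is claimed about the consent form. No estimate, sample size or analysis is affected. Low severity; a cheap improvement.

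**What to change.** Replace the sentence under Participant Confidentiality and Security with wording such as:

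> Individual results of the coded research assays (microbiota, fecal water content and total protein, IAP, immunoglobulins, MG-H1, and any later analyses of stored serum and research DNA) are not returned to participants. Clinically relevant abnormal results from the hospital laboratories, including fecal calprotectin, are passed by the study clinician to the participant or guardian and, where appropriate, to the treating physician.

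If the participant information carries the same sentence, change it there too. The cost is the wording change and a little time from the clinician who already meets every participant. No new test or visit is needed.

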**Study Discontinuation**

Participants have the right to withdraw their consent at any time without giving a specific explanation. If they withdraw the consent, their samples and personal data or other data will no longer be used in the research project. Refusing consent or withdrawing it later does not affect the availability of healthcare services.

